### 2.3. Registration and Randomization

The patient code consists of the number of the contributing center (one digit), followed by a letter for the treatment approach (R = radiotherapy alone, S = radiotherapy plus systemic treatment) and a consecutive number consisting of 3 digits. Example: 1R-001.

Patients will be randomized 1:1 to receive either standard treatment for lung cancer supported by the “Step Reminder” app (Arm A) or standard treatment for lung cancer without the app (Arm B) using a block randomization scheme. Randomization is stratified according to presence or absence of concurrent systemic therapy (yes vs. no) [23]. The randomization list is going to be provided by an external professional statistician. The information regarding randomization (Arm A or Arm B) will be obtained from the department of the principal investigator. Study personnel will provide standardized instructions regarding smartphone handling to all participants to ensure consistent data collection conditions across study sites.

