### 2.5. Statistics

#### 2.5.1. Sample Size

This prospective randomized study is designed to analyze the effect of the “Step Reminder” app on physical activity during irradiation in lung cancer patients. The primary endpoint is the within-patient change in weekly average steps per wear-hour between the fifth and the first week. The primary analysis includes all randomized patients with evaluable data regarding the primary endpoint. The comparison (“Step Reminder” app group vs. control group) is made with a two-sided Wilcoxon–Mann–Whitney U test.

Calculation of the required sample size considers a clinically relevant difference corresponding to a relative difference in the within-patient change in steps per wear-hour of about 30% between treatment arms. Given the non-parametric nature of the primary analysis, this assumption is interpreted as a moderate shift in the distribution of the endpoint, which represents a probability of superiority of about 0.65. The assumed 30% relative difference represents a pragmatic planning assumption for this exploratory randomized phase 2 trial and should not be interpreted as an established minimal clinically important efficacy difference for this endpoint. Assuming a two-sided significance level of α = 0.05 and a statistical power of 80%, 28 patients are needed to detect such an effect using the asymptotic approximation of the Wilcoxon–Mann–Whitney U test. It is assumed that approximately 10% of the randomized patients cannot be evaluated with respect to the primary endpoint. Therefore, 32 patients need to be randomized. The calculation aligned with the analysis population, and the endpoint definition is considered appropriate for this exploratory study. The multicenter design primarily supports recruitment feasibility and broader applicability of the exploratory findings; it is not intended to imply a confirmatory multicenter efficacy trial. Results are interpreted descriptively and will contribute to the design of additional larger studies.

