Statistical analysis is based on observed cases only. Patients must meet the predefined criteria for valid data in week 1 and week 5 to be included in the primary analysis. Missing data, if any, may be expected to be not missing completely at random, particularly in relation to insufficient smartphone wear time. Therefore, the extent and patterns of missing data will be described descriptively, and reasons for non-evaluable data will be summarized. Because of the small sample size and the exploratory nature of the APPAREL trial, no formal imputation and no best-case, worst-case, or model-based missing-data sensitivity analyses will be performed. The predefined approach for missing primary endpoint data is restricted to complete-case analysis, and the results are interpreted in light of the observed missing data structure. The per-protocol set is analyzed using the same statistical methodology as for the primary analysis. Results from the per-protocol set are considered supportive and will be used to assess the consistency and robustness of the findings in the full analysis set. Statistical tests are performed as two-sided tests with a nominal significance level of α = 0.05. Given the exploratory nature of this randomized trial, no adjustment for multiplicity is applied, and *p*-values beyond the primary endpoint analysis are interpreted descriptively. All secondary, subgroup, adjusted, and sensitivity analyses will be interpreted descriptively. Nominal *p*-values from these analyses will not be interpreted as confirmatory.

All available data will be used irrespective of adherence to the assigned treatment, including non-use or discontinuation of the reminder app, provided that sufficient data are available for endpoint calculation. Exploratory adjusted analyses may be performed to account for potential baseline imbalances, including baseline physical activity and the stratification factor (concurrent systemic treatment: yes vs. no). These analyses can be interpreted as supportive. Fatigue, pain, distress, and performance status will be summarized descriptively and may be explored in supportive analyses to contextualize changes in physical activity. They are not included as mandatory covariates in the primary model due to the small sample size and the risk of overfitting.

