#### 2.5.3. Statistical Aspects Related to the Primary Endpoint

Primary analysis is performed in the full analysis set and compares the distribution of within-patient changes between the treatment groups (“Step Reminder” app vs. control). No imputation of missing data is performed. The analysis is based on observed cases only. Extent and pattern of missing data are described descriptively. The primary estimand is directed at the difference between treatment groups in the average within-patient change in physical activity between the fifth and the first week. Intercurrent events, including incomplete smartphone use, technical failures, or treatment interruptions, are addressed using a treatment policy strategy, where available, valid data are included without imputation. Descriptive statistics of the primary endpoint will be provided by treatment group, including the number of subjects with evaluable data, mean (plus standard deviation), and median (plus quartiles, minimum, and maximum). Individual patient trajectories are visualized using spaghetti plots. The endpoint represents a normalized activity metric and is intended to account for heterogeneity in device usage and to reduce bias associated with unequal observation periods. Wear-time has been shown to influence estimates derived from consumer-grade wearable data, supporting the need to account for device usage time in digital physical activity analyses.

The primary comparison between treatment groups is performed with the two-sided Wilcoxon–Mann–Whitney U test. The magnitude of the treatment effect is estimated using the Hodges–Lehmann estimator together with a two-sided 95% confidence interval. Given the limited sample size, the results are interpreted descriptively only. A paired *t*-test may be reported as an additional analysis if the distribution of within-patient differences is approximately normal.

Within each treatment group, the change between week 1 and week 5 is analyzed using the Wilcoxon signed-rank test. A paired *t*-test may be provided as a supportive analysis if appropriate. If diagnostic checks indicate substantial skewness, a supportive analysis on the log scale is performed, and results are expressed as ratios of geometric means with corresponding 95% confidence intervals, without changing the primacy of the analysis on the original scale.

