
One has to be aware that other important prognostic variables, such as age, performance status, baseline physical activity, histology, disease burden, and type of smartphone, are not incorporated into the primary analysis. Concurrent systemic treatment was selected as the only randomization stratification factor, since it is expected to have a strong impact on fatigue, toxicity, and physical activity, and since additional stratification factors appear impractical and potentially unstable with only 32 randomized patients. Other baseline characteristics, including age, performance status, histology, distress, pain, and fatigue, will be summarized descriptively and evaluated in exploratory analyses only. One has to be aware that the effect size of 30% has been chosen after discussion with experienced radiation oncologists, medical oncologists, and pulmonologists, but is not supported by clinical evidence. No validated minimal clinically important difference currently exists for normalized step-count endpoints in patients receiving thoracic radiotherapy.

The question may arise why the step counts are limited to weeks 1 and 5. These weeks were selected pragmatically to compare early-treatment activity with activity near the end of conventionally fractionated radiotherapy, while minimizing the burden for the patients and staff members. Due to this approach, intermediate fluctuations will not be captured, which limits the interpretation of temporal trajectories. Satisfaction and digital health adoption outcomes are secondary descriptive endpoints only; they are intended to assess usability, acceptability, and feasibility, not to test formal inferential hypotheses.

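### The primary rank test ignores the factor that randomization is stratified on, and the adjusted analysis that would use it is only optional

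*Protocol article*

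**What the plan says.** Section 2.3 of the protocol article: "Randomization is stratified according to presence or absence of concurrent systemic therapy". The Discussion (section 3) justifies this as the only stratification factor, because it is expected to act strongly on fatigue, toxicity and physical activity.

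Section 2.5.1: "The primary endpoint is the within-patient change in weekly average steps per wear-hour between the fifth and the first week". Section 2.5.3: "The primary comparison between treatment groups is performed with the two-sided" Wilcoxon–Mann–Whitney U test, with a Hodges–Lehmann estimate and 95% confidence interval. No stratum or covariate enters either.

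Section 2.5.2: "Exploratory adjusted analyses may be performed to account for potential baseline imbalances, including baseline physical activity and the stratification factor". These analyses are described as supportive. The Discussion lists prognostic variables left out, among them "baseline physical activity, histology, disease burden, and type of smartphone, are not incorporated into the primary analysis".

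Section 2.5.3 adds an exploratory mixed model with time, treatment, their interaction and a random patient intercept, again without the stratum.

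**The concern.** Stratified randomization balances the arms on concurrent systemic therapy, so the true variance of the arm contrast no longer contains the between-stratum part. A test that ignores the stratum still counts that part as noise. It therefore rejects too seldom and gives up power, which is costly with about 14 patients per arm.

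Adjustment for the stratum and for starting activity is named but not fixed. An analysis that may be performed can be reported or dropped once the data are seen. The mixed model does not fill the gap: with two complete time points its interaction is the same difference in change scores.

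**Working it through.** **Inputs.** 28 evaluable patients, 1:1, two-sided α = 0.05, 80% power, probability of superiority 0.65 (section 2.5.1). The article gives neither the effect of the stratum on change nor the week 1–week 5 correlation ρ. Both are assumptions below, shown as ranges where possible.

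**1. The plan's own figure.** Noether's formula for the Wilcoxon–Mann–Whitney test gives N = (1.960 + 0.842)² / (12 × 0.25 × 0.15²) = 7.849 / 0.0675 = 116.3, so 117 in total, not 28. At N = 28, power is Φ(√(3 × 28) × 0.15 − 1.960) = Φ(−0.585) = 28%. The step from 28 to 32 does reproduce (28 / 0.9 = 31.1, rounded up). The shortfall is a separate and larger fault; here it sets the level against which any gain is read.

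**2. Leaving out the stratum.** For normal data, 0.65 corresponds to d = √2 × z(0.65) = 0.545 SD of the within-stratum change. Assume strata of equal size and a stratum shift of 1 SD. The pooled variance is 1 + 0.5 × 0.5 × 1² = 1.25, while the true sampling variance of the contrast stays at its within-stratum value.

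- Stratified: expected Z = 0.545 × √7 = 1.442; power = P(Z > 1.960 − 1.442 = 0.518) = 30%.
- Unstratified: expected Z = 1.442 / √1.25 = 1.290, with SD 1 / √1.25 = 0.894; power = P(Z > (1.960 − 1.290) / 0.894 = 0.75) = 23%.
- Unstratified type I error: P(|Z| > 1.960 / 0.894 = 2.19) = 2.8%.

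Simulation of the rank tests (14 per arm, normal data, arms balanced within strata) puts both powers a little lower: about 17% to 20% for Wilcoxon–Mann–Whitney and about 25% to 27% for van Elteren, depending on run and on the stratum split (14/14 or 8/20). Type I error is about 2% to 3% and about 5%, respectively. With a 0.5 SD stratum shift the powers are about 24% and 26% to 27%. With no shift they are about 25% to 26% and 26% to 27%, so stratifying costs nothing visible.

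**3. Adjusting for week-1 activity.** With equal week-1 and week-5 variances, the ANCOVA variance relative to the change score is (1 + ρ)/2 × 25/24, the last factor being the small-sample cost at N = 28.

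| ρ | Ratio | Reduction in variance |
|---|---|---|
| 0.5 | 0.78 | 22% |
| 0.7 | 0.89 | 11% |
| 0.8 | 0.94 | 6% |
| 0.9 | 0.99 | 1% |

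If the week-5 SD is 1.25 times the week-1 SD, the ratio is 1.5625 × (1 − ρ²) / (2.5625 − 2.5ρ) × 25/24. At ρ = 0.5 this is 0.93 (7% lower); at 0.7 and 0.8 there is no gain. A smaller week-5 SD would raise the gain.

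Simulated power for Wilcoxon on change against ANCOVA, normal data, at 0.65: 25% vs 34% (ρ = 0.5), 25% vs 32% (0.7), 26% vs 31% (0.8). With lognormal data, Wilcoxon against rank ANCOVA: 28% vs 34%, 25% vs 29%, 23% vs 25%. Linear ANCOVA on the raw skewed values gains nothing at 0.7 (25% vs 25%) or 0.8 (23% vs 23%).

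**4. Week 1 is not a true baseline.** Steps are taken from weeks 1 and 5 of radiotherapy only (section 2.4.2, Table 1), and the app reminds patients throughout that course (section 2.4.3). If the app shifts both weeks by the same amount s, the difference in change is zero, but ANCOVA estimates (1 − ρ)s. At ρ = 0.5 and 14 per arm, simulated rejection by ANCOVA is about 10% to 12% for s = 0.5 SD and about 26% to 27% for s = 1 SD. Wilcoxon on change stays at about 4% to 5%.

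**The case against.** An unstratified Wilcoxon–Mann–Whitney test remains valid under this randomization; it errs on the conservative side. The article names both covariates, discloses in the Discussion that starting activity is left out, calls the trial exploratory and reads its results descriptively. Details of supportive models are often left to an analysis plan. All this stands and lowers the stakes. It does not cover the primary test, which the article itself fixes without the stratum.

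The stratum may also act on the level of activity in both weeks alike, in which case the change score already removes it. That is possible, and the gain would then be about nil. The cost would be about nil too.

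Three stronger readings are tempting and not supported:

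- A reader might infer that ANCOVA on week-1 activity should be the primary test because the precision is free. Section 2.5.3 targets the difference in change, and week 1 falls after randomization with the app active. If the app already acts in week 1, that analysis answers another question, and its rejection rate for zero difference in change can be well above 5%.
- A reader might infer that the article rejects starting activity as a covariate for fear of overfitting. The sentence "They are not included as mandatory covariates in the primary model due to the small sample size and the risk of overfitting" refers to fatigue, pain, distress and performance status. No such reason is given for starting activity or the stratum.
- A reader might infer that adjustment would rescue the sample size. By the normal approximation, power at 0.65 with week-1 adjustment is 37% at ρ = 0.5 and 30% at 0.9.

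**Conclusion.** The point holds for the stratum. The primary test leaves out a factor that the trial randomizes on, already records and expects to matter. The loss is roughly 7 to 8 percentage points of power at 0.65 if the stratum shifts the change by 1 SD, about 2 to 3 points at 0.5 SD, and close to nothing without a shift. These figures assume normal data, 14 per arm and an app effect common to both strata.

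For week-1 activity the point is narrower. The optional wording should become a fixed supportive analysis, but its gain (22% down to 1% lower variance for ρ from 0.5 to 0.9, with equal variances) rests on a correlation the article does not give, and it shrinks with skewed data or a larger week-5 variance. Because week 1 is measured under treatment, this analysis cannot replace the primary test without changing the estimand.

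**What to change.** 1. In section 2.5.3, run the primary comparison as a rank test stratified by concurrent systemic therapy, for example van Elteren, with a stratified or aligned Hodges–Lehmann estimate and 95% confidence interval. State what is done if a stratum is very small or has patients in one arm only. The estimand is unchanged and no new data are needed: the patient code in section 2.3 already carries the stratum.

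2. In section 2.5.2, replace the optional wording by one named supportive analysis, always reported with its 95% confidence interval: rank-based or log-scale ANCOVA on week-1 activity and stratum. Leave the other covariates exploratory.

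3. Beside it, state that week 1 is after randomization with the app active, so that, if the app already shifts week 1, this analysis targets something other than the difference in change.

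The cost is wording and a few lines of analysis code. A starting value untouched by the app would need a step count before treatment, which Table 1 does not include; that would be a design change, not part of this fix. The sample-size statement needs its own correction.

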#### 2.5.3. Statistical Aspects Related to the Primary Endpoint

Primary analysis is performed in the full analysis set and compares the distribution of within-patient changes between the treatment groups (“Step Reminder” app vs. control). No imputation of missing data is performed. The analysis is based on observed cases only. Extent and pattern of missing data are described descriptively. The primary estimand is directed at the difference between treatment groups in the average within-patient change in physical activity between the fifth and the first week. Intercurrent events, including incomplete smartphone use, technical failures, or treatment interruptions, are addressed using a treatment policy strategy, where available, valid data are included without imputation. Descriptive statistics of the primary endpoint will be provided by treatment group, including the number of subjects with evaluable data, mean (plus standard deviation), and median (plus quartiles, minimum, and maximum). Individual patient trajectories are visualized using spaghetti plots. The endpoint represents a normalized activity metric and is intended to account for heterogeneity in device usage and to reduce bias associated with unequal observation periods. Wear-time has been shown to influence estimates derived from consumer-grade wearable data, supporting the need to account for device usage time in digital physical activity analyses.

The primary comparison between treatment groups is performed with the two-sided Wilcoxon–Mann–Whitney U test. The magnitude of the treatment effect is estimated using the Hodges–Lehmann estimator together with a two-sided 95% confidence interval. Given the limited sample size, the results are interpreted descriptively only. A paired *t*-test may be reported as an additional analysis if the distribution of within-patient differences is approximately normal.

Within each treatment group, the change between week 1 and week 5 is analyzed using the Wilcoxon signed-rank test. A paired *t*-test may be provided as a supportive analysis if appropriate. If diagnostic checks indicate substantial skewness, a supportive analysis on the log scale is performed, and results are expressed as ratios of geometric means with corresponding 95% confidence intervals, without changing the primacy of the analysis on the original scale.

As a further exploratory supplementary analysis, a linear mixed-effects model is fitted, including fixed effects for time (week 1, week 5), treatment (“Step Reminder” app vs. control), and their interaction, as well as a random intercept for the patient. The treatment-by-time interaction represents the difference between treatment groups in the change from week 1 to week 5. Results from this model are reported as point estimates, two-sided 95% confidence intervals, and descriptive *p*-values. They have to be interpreted cautiously due to the limited sample size. If appropriate, a log-transformed analysis is provided as a sensitivity analysis.

Exploratory subgroup analyses may be conducted to assess whether the treatment effect differs across subgroups, namely age category, performance status, histology, concurrent systemic treatment, and type of smartphone (iOS vs. Android). Given the small overall sample size and the resulting low numbers within subgroups, these analyses can only be regarded as exploratory and hypothesis-generating.

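### Randomisation is stratified by concurrent systemic therapy but the primary rank test and interval ignore it; if the stratum predicts the change in activity, the test is conservative and loses power.

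*Protocol article*

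**What the plan says.** - **Randomisation (2.3).** Allocation is 1:1 in blocks, and "Randomization is stratified according to presence or absence of concurrent systemic therapy (yes vs. no"). It is the only stratification factor.
- **Why this factor (Discussion).** It was chosen "since it is expected to have a strong impact on fatigue, toxicity, and physical activity".
- **Primary test (2.5.3).** "The primary comparison between treatment groups is performed with the two-sided" Wilcoxon–Mann–Whitney U test, applied to the within-patient change. The effect is estimated by Hodges–Lehmann with a 95% interval. Neither is described as stratified.
- **Where the stratum appears (2.5.2, 2.5.3).** "Exploratory adjusted analyses may be performed to account for potential baseline imbalances, including baseline physical activity and the stratification factor"; these are supportive only. It is also one of the optional subgroups. The supplementary mixed model has time, treatment, their interaction and a patient intercept, but no stratum.
- **Reasons given for leaving variables out.** The overfitting argument in 2.5.2 names fatigue, pain, distress and performance status. The Discussion says that other prognostic variables are absent from the primary analysis. Neither statement covers the stratification factor.

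**The concern.** Stratified randomisation forces the arms to be nearly balanced on systemic therapy. An unstratified rank test computes its variance as if that balance had been left to chance. If the two strata differ in their mean change, the difference between them stays in the reference variance although it can hardly move the arm comparison. The p-value then tends to be too large and the interval too wide, and more so the stronger the stratum effect.

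The protocol itself expects a strong effect on activity, has few patients, and wants an estimate that can inform larger trials. Overfitting is no reason to leave the stratum out, because a stratified rank test estimates no covariate coefficient.

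**Working it through.** **Inputs from the protocol.** 28 evaluable patients, taken as 14 per arm; two-sided alpha 0.05; probability of superiority 0.65 (2.5.1); one binary stratum (2.3).

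**Assumptions.** Normal errors with SD 1; stratum difference in the mean change, γ, from 0 to 2 SD; strata of 14+14, 20+8 or 24+4 patients (7/7, 10/4 or 12/2 per arm), balanced between arms. The protocol gives neither γ nor the split.

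**1. The plan's own figure.** Noether's formula for the total sample is N = (z_α/2 + z_β)² / [12 × 0.25 × (P − 0.5)²] = (1.960 + 0.842)² / (3 × 0.15²) = 7.849 / 0.0675 = 116.3, so 117 and not 28. At N = 28 the power is Φ(√(3 × 28) × 0.15 − 1.960) = Φ(−0.585) = 28%. The dropout step does reproduce: 28 / 0.9 = 31.1, so 32. The sample size is a separate problem. It matters here only because it shows how little power there is to lose.

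**2. Effect on alpha, by approximation.** With π the share of patients in one stratum, the variance of the change that the unstratified test sees is 1 + π(1 − π)γ². The part relevant to the balanced comparison is 1. So true alpha ≈ 2Φ(−1.960 × √[1 + π(1 − π)γ²]).

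- Equal strata, γ = 1: √1.25 = 1.118, giving 2Φ(−2.191) = 0.028.
- Equal strata, γ = 0.5: √1.0625 = 1.031, giving 2Φ(−2.020) = 0.043.
- 20+8, γ = 1: √1.204 = 1.097, giving 2Φ(−2.151) = 0.031.

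**3. Simulation.** The van Elteren statistic is T = Σ W_k/(N_k + 1), with mean Σ m_k/2 and variance Σ m_k(N_k − m_k)/[12(N_k + 1)]. Here W_k is the Arm A rank sum, m_k the number in Arm A and N_k the total in stratum k. The within-stratum shift is √2 × Φ⁻¹(0.65) = 0.545 SD. Neither test has a continuity correction; 40,000 runs per cell.

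| Strata | γ (SD) | Alpha, unstratified | Alpha, stratified | Power, unstratified | Power, stratified |
|---|---|---|---|---|---|
| 14+14 | 0 | 0.051 | 0.052 | 27% | 27% |
| 14+14 | 0.5 | 0.044 | 0.052 | 25% | 27% |
| 14+14 | 1 | 0.028 | 0.051 | 19% | 26% |
| 14+14 | 2 | 0.005 | 0.050 | 7% | 27% |
| 20+8 | 0 | 0.048 | 0.048 | 27% | 26% |
| 20+8 | 0.5 | 0.045 | 0.048 | 26% | 26% |
| 20+8 | 1 | 0.033 | 0.049 | 21% | 26% |
| 24+4 | 0 | 0.051 | 0.049 | 27% | 26% |
| 24+4 | 0.5 | 0.046 | 0.047 | 26% | 26% |
| 24+4 | 1 | 0.038 | 0.046 | 23–24% | 25% |

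Repeat runs move these figures by about one point. Before rounding, the planned test is slightly ahead at 24+4 and 0.5 SD (26.1% against 25.5%). With blocks of 4 and 4 of 32 patients lost at random, γ = 1 gives alpha 0.030 against 0.049 and power 20% against 26%. For a large treatment effect (1.1 SD) with equal strata and γ = 1, power is 69% against 77%.

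**4. Mixed model.** With two weeks per patient, the treatment-by-time term is the difference in mean change, and a stratum effect that is constant over time cancels out of it. In a simulated data set the standard error was 0.436 both with and without a stratum main effect, and 0.389 once a stratum-by-time term was added.

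**The case against.** **The loss is conditional.** A reader might infer that the trial's p-values and intervals will certainly be wrong. The documents do not support that. They expect an impact on physical activity, not specifically on the change, and give no size. Week 1 is already a treatment week, so any stratum difference present in both weeks cancels. The 1 SD case is an assumption. This stands, and the point is worded accordingly.

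**The planning effect is defined for the arms overall.** With γ = 1 and equal strata, a within-stratum shift of 0.545 SD corresponds to an overall probability of superiority of about 0.635. At an overall 0.65 (shift about 0.61 SD) the powers are 24% and 32%. The levels rise, but the gap remains.

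**Consequences are limited.** The error is conservative, so a reader who inferred a false-positive risk would be mistaken. Section 2.5.3 says that results are read descriptively, and 2.5.2 already permits an adjusted analysis. This lowers the severity. It does not remove the point: under a descriptive reading the interval is the main product, and an analysis that may be done is not a prespecified one.

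**Stratifying does not rescue the trial.** True: power stays near 26% at the within-stratum shift of 0.545 SD.

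**Conclusion.** The mismatch is in the text and is not explained: the one factor used to stratify randomisation is missing from the primary test and interval. The direction of the consequence is certain if the stratum predicts the week 5 minus week 1 change; its size is not known.

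At an assumed 1 SD stratum difference, alpha falls to about 3–4% and power drops by about 7 points with equal strata, 5 points with a 10/4 split per arm, and 1 to 2 points with a 12/2 split. At 0.5 SD the difference is 2 points or less in either direction. With no stratum effect, stratifying costs 0 to 2 points.

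These figures rest on normal errors, near-balanced strata and 28 evaluable patients. This is a worthwhile improvement to an exploratory trial, not a flaw that invalidates its result.

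**What to change.** In 2.5.3, make the primary comparison the van Elteren (stratified Wilcoxon) test by concurrent systemic therapy. Use a within-stratum permutation p-value, because the strata will be small, and a stratum-aligned Hodges–Lehmann estimate with 95% confidence interval. Keep the unstratified test and estimate as a sensitivity analysis.

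In the supplementary mixed model, add the stratum together with its interaction with time; a main effect alone would change nothing of interest.

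The cost is wording only, with no extra patients or data. The downside is up to about 2 points of power if the stratum has no effect or one stratum is very small. The sample size needs its own correction.
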